**Fig. 3 Fig3:**
[figure not shown]
Expected distribution of patients according to the stepped-wedge design

Moreover, all 5 participating regions outside Basse-Normandie candidates for training their caregivers to TPE, will each include 15 assessable patients in the control group (before being trained). It will be therefore possible to compare, at the region scale, the effect of TPE implementation on daily activities.

To meet to the objective of the Step 4, the judgement criterion is the proportion of patients recruited in Basse-Normandie area adhering to the whole PEP.

Under the assumptions of p_0_ = 0.70, p_1_ = 0.85, α = 5%, and β = 10%, 80 patients are necessary (unilateral exact binomial test that compares a proportion to a reference value) in order to best characterize adhesion to the PEP in the region (Fig. 3).

Of these patients, 15 will be randomly assigned for participation of Basse-Normandie in the primary objective (Step 5 of the study).

Overall, 230 evaluable patients are required; it is therefore planned to recruit 260 patients in order to anticipate some non-assessable patients.

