### Statistical analysis

#### Sample size calculation

The calculation of the number of subjects needed for statistical significance is based on the main judgement criterion and on the first secondary endpoint.

To meet the first primary objective (Step 5 of the study) building on a stepped-wedge design, the calculation of needed number of patients is based on a ≥ 2-point decrease of the mean score of the BPI subscale 9 at 8 weeks after inclusion, in the experimental PEP group compared to the control group (corresponding to a clinically significant improvement). The calculation takes into account that randomisation is done by clusters (patients belonging to a same cluster are not independent). Based on bilateral test and common-factor variances (2.5-point standard deviation in both groups (intraclass correlation coefficient = 0.05; 3 clusters per randomisation arm; alpha = 5%; power = 80%) it is estimated that 45 patients per arm equitably distributed between the 6 clusters, for a total of 90 assessable patients (Fig. 3).

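### The claim that the TPE effect can be compared at region scale does not fit the design: within one region, programme and calendar time cannot be separated

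*Protocol article*

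**What the plan says.** In the section Sample size calculation, in the text after Fig. 3, the article says of the five regions outside Basse-Normandie that they "will each include 15 assessable patients in the control group (before being trained". From this it draws a conclusion: "It will be therefore possible to compare, at the region scale, the effect of TPE implementation on daily activities".

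The section Study design fixes the order of care. An outside centre gives conventional care until its staff are trained and the educational approach afterwards. Basse-Normandie is already trained and contributes PEP patients only.

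The section Data analysis describes a first comparison of 8-week scores between PEP and control by a mixed model that allows for correlated data. It then describes a global mixed model that accounts for period, cluster and the type of care given. The global model is the only analysis for which period is named. No analysis of a single region is described, and no power, significance level or time adjustment is given for one.

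**The concern.** A stepped-wedge trial can separate an intervention from time because its clusters switch at different moments: in a given period, some clusters are still in control while others have crossed over. One region on its own has no such concurrent comparison. Having its own pre-training controls gives it a before-after contrast, not an estimate of the effect of TPE.

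The sentence therefore credits the design with a property it lacks. Someone relying on it could report a region's improvement as programme benefit when it reflects a change over time in case mix, analgesic practice or staffing. Equally, an unremarkable contrast in a small region could be reported as absence of benefit. The primary estimate and the planned sample size are not touched.

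**Working it through.** **1. The plan's own figure.** The inputs come from Sample size calculation: a difference of 2 between the arms ("≥ 2-point decrease of the mean score of the BPI subscale 9 at 8 weeks after inclusion, in the experimental PEP group compared to the"); the spread ("2.5-point standard deviation in both groups"); two-sided testing ("Based on bilateral test and common-factor variances"); and, for the remaining inputs, "intraclass correlation coefficient = 0.05; 3 clusters per randomisation arm; alpha = 5%; power = 80" (per cent).

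- Individual n per arm, normal approximation: 2 × [2.5 × (1.960 + 0.842) / 2]² = 24.5, so 25. The t-test version needs 25.5, so 26.
- Design effect with 15 per cluster: 1 + (15 − 1) × 0.05 = 1.7.
- 26 × 1.7 = 44.2, which as three clusters of 15 gives 45. This agrees with "45 patients per arm equitably distributed between the 6 clusters, for a total of 90 assessable patients". (The normal approximation gives 24.5 × 1.7 = 41.7 to 25 × 1.7 = 42.5.)

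So the difference of 2 and SD of 2.5 can be carried over to a single region.

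**2. What one region can identify.** Let μ be the mean under control before training, τ the change over calendar time and θ the effect of TPE.

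- Before training: expected score μ.
- After training: expected score μ + τ + θ.
- Contrast: τ + θ.

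The design rows (intercept, after-training period, PEP) are (1, 0, 0) and (1, 1, 1). Their rank is 2 for 3 parameters, so τ and θ cannot be separated at any sample size. Dividing each phase into more periods does not help, because the PEP indicator is then the sum of the post-training period indicators. Only an assumed shape for the time trend would separate them, and the article states none for a regional analysis.

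The bias equals τ. The documents give no value. If a shift of 0.5 to 1 point is assumed, it would pass for 0.5/2 = 25% to 1/2 = 50% of the 2-point target.

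**3. Patients per region.** The 15 controls are stated. The number of PEP patients is not stated in the text, and Fig. 3 is not shown in the copy reviewed. It can be inferred: "Overall, 230 evaluable patients are required", of whom 80 are in Basse-Normandie and 5 × 15 = 75 are outside controls. That leaves 230 − 80 − 75 = 75, or 75/5 = 15 per region.

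**4. Precision of 15 versus 15** (difference 2, SD 2.5, two-sided 5%, unadjusted):

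- SE = 2.5 × √(2/15) = 0.913.
- 2/0.913 = 2.19; 2.19 − 1.96 = 0.23; power = Φ(0.23) = 59% (normal), or 56% (t, 28 df).
- Approximate 95% interval half-width: 1.96 × 0.913 = 1.79 points.
- For 80% power: about 26 per group, or a difference of about 2.65 points with 15 per group.

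**5. Sensitivity of the power figure.**

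| Variation | Power |
|---|---|
| Within-cluster SD, 2.5 × √0.95 = 2.44 | 58% (t), 61% (normal) |
| Baseline-adjusted, assumed correlation 0.3 | 60% (t) |
| Baseline-adjusted, assumed correlation 0.5 | 69% (t) |
| Baseline-adjusted, assumed correlation 0.7 | 84% (t) |

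The baseline correlation is an assumption; the article gives none. None of these variations changes step 2.

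**The case against.** The strongest reply is that no regional analysis is planned. Region-by-region effectiveness is not among the objectives, the endpoints or the listed analyses. The sentence only says that a comparison will be possible, and the article already accounts for period in its global model. This stands in large part and limits the point to one statement. It does not rescue that statement, which says that the effect of TPE can be compared at region scale and rests this on each region's own controls. A separate analysis plan could add detail but could not make the statement true.

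A second reply is that region scale may mean the five before-after contrasts taken together. That reading is possible. On it the power remark falls away: 75 versus 75 has over 99% power if clustering and time are ignored. Time would still have to be modelled across clusters. The region-by-region reading is the more natural one, because the conclusion follows directly from what each region includes.

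Third, the power figure depends on inferred PEP numbers and an unadjusted analysis. This is correct. Baseline is measured and the global analysis is covariate-adjusted, so power below 60% is one case and not a fixed property.

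A reader might also infer a multiplicity error: five independent tests at 5% give 1 − 0.95⁵ = 22.6% for at least one false positive. The documents do not support that charge. They specify no regional test, and the section Data analysis refers to an overall 5% error level.

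**Conclusion.** The point holds as a minor one about a single sentence. Read region by region, the claim is wrong for this design: the contrast within a region is fully confounded with calendar time, whatever the number of patients. This rests only on the order of care given in Study design.

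The precision remark is secondary. Power is about 56% to 59% if there are 15 PEP patients per region and the test is unadjusted and two-sided with the planning difference and SD. It is about 60% to 84% with baseline adjustment at assumed correlations of 0.3 to 0.7.

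A reader might go further and conclude that the trial will run five underpowered regional tests, or that its main effect estimate ignores time. Neither follows. No regional tests or regional power are stated, and the global model includes period.

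**What to change.** Reword the sentence so that regional before-after contrasts are descriptive only, shown with confidence intervals and without regional tests or claims of effect. State alongside it that the effect of TPE is estimated from the period-adjusted global mixed model across clusters.

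A treatment-by-cluster term could be added to describe heterogeneity between centres, but this is optional. Only five clusters switch, since Basse-Normandie has no control phase, so the variance of that term would be poorly estimated.

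The cost is a change of wording and giving up stand-alone regional effect claims. Recruitment, sample size and the primary analysis do not change.

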## Methods/design

### Study design

The impact and benefit of the PEP will be evaluated by comparing the educational approach and the “conventional” management of pain. The Step 5 of the EFFADOL project is a multicentre, stepped-wedge, cluster randomised controlled trial. This particular randomised design known as the step-wedge procedure [17–19] minimize the risk of contamination between the two groups (conventional vs TPE approach) and thereby the risk of bias. Indeed, when the purpose is to compare two practices (in this case, TPE and conventional care) in which the attitudes of the caregivers are changed, it is critical to set up at the same time, and with the same health staff the two assessed different modes of care. The stepped-wedge design particularly suits in such setting since it makes it possible to stagger the training of the caregivers hospital by hospital and consequently that of the educational intervention per participating centre. The randomisation is performed at the cluster level, instead of the patient level.

Thus, 6 clusters will be formed in which TPE dispensing will be strictly identical. The first cluster includes 11 participating centres from Basse-Normandie where enrolled patients will all receive the educational approach as healthcare (physician/nurse) staff at the regional level have been already trained in TPE (Step 1 of the EFFADOL project). Then, five other clusters that correspond to five participating centres outside the region at the national level will be gradually included in a stepped-wedge design (Fig. 1). Finally, the conventional approach (before training) will be compared to the educational approach (after being trained).

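### Basse-Normandie cannot be a randomised cluster, yet it is counted as one of six and enters the primary comparison through a random draw of 15 of its 80 patients

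*Protocol article*

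**What the plan says.** Under Study design the article states: "The randomisation is performed at the cluster level, instead of the patient level". It then describes two kinds of cluster. On Basse-Normandie: "The first cluster includes 11 participating centres from Basse-Normandie where enrolled patients will all receive the educational approach", because its staff "have been already trained in TPE (Step 1 of the EFFADOL project"). On the rest: "five other clusters that correspond to five participating centres outside the region at the national level will be gradually included in a stepped-wedge design".

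The Sample size calculation takes a 2-point effect, SD 2.5, ICC 0.05, two-sided alpha 5%, 80% power and "3 clusters per randomisation arm". It arrives at "45 patients per arm equitably distributed between the 6 clusters, for a total of 90 assessable patients". After Fig. 3 it adds 15 control patients in each of the five outside regions and sets 80 Basse-Normandie patients for the Step 4 adherence question. On those 80 it says: "Of these patients, 15 will be randomly assigned for participation of Basse-Normandie in the primary objective (Step 5 of the study").

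Data analysis first compares PEP with control in a mixed model that allows for correlated data. It also plans a global mixed model with periods, clusters and care provided, adjusted for patient characteristics. Neither description sets Basse-Normandie apart, and neither says whether cluster is a fixed or a random effect.

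**The concern.** A cluster whose staff were trained before the trial has its place fixed by history. It cannot be allocated to a later step and has no before-training period. Basse-Normandie therefore adds patients to the PEP side and none to the control side, and its contrast with the other clusters is not protected by randomisation. The Discussion relies on exactly that protection when it gives cluster randomisation as a way to control confounding.

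The region also differs from the others in ways the article itself describes. It is where the programme was built, and it pools 11 centres where every other cluster is a single centre. A difference in pain interference that comes from these features, and not from the programme, can pass into the estimated effect.

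The draw of 15 does not help with this. It gives the region no comparator. It leaves most of its patients out of the primary comparison, and it makes the estimate depend on which 15 are chosen. A mixed model does not need equal cluster sizes.

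**Working it through.** **1. The plan's own figures.** Inputs from the Sample size calculation: effect 2, SD 2.5, ICC ρ = 0.05, k = 3 clusters per arm, two-sided 5%, power 80%.

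- Without clustering, the two-sample t-test at 2/2.5 = 0.8 SD needs 25.5, so n = 26 per arm.
- With k clusters per arm, m = n(1 − ρ)/(k − nρ) = 26 × 0.95/(3 − 1.3) = 24.7/1.7 = 14.5, so 15 per cluster.
- 3 × 15 = 45 per arm, 90 in total. This matches the plan.
- 90 + 5 × 15 controls + (80 − 15) = 90 + 75 + 65 = 230. This also matches.

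The 45 per arm is thus a parallel three-against-three calculation, and six clusters are reached only by counting Basse-Normandie.

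**2. What Basse-Normandie contributes.** On the reading that gives 230, the primary comparison has 15 Basse-Normandie PEP patients, 75 PEP patients elsewhere and 75 controls. Basse-Normandie supplies 15/90 = 17% of the PEP patients and 0 of 75 controls.

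**3. Effect of a non-programme difference.** The period layout is not available in the text, so these layouts are assumptions: six periods, one outside centre crossing per step, Basse-Normandie on PEP in all six.

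- Layout A: each outside centre has 15 control and 15 PEP patients, spread evenly over its control and PEP periods.
- Layout B: 5 patients per outside centre per period, again 75 control and 75 PEP in all.

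The estimator is generalised least squares, (X′V⁻¹X)⁻¹X′V⁻¹y. X holds treatment and period terms. V has between-cluster variance ρ × 2.5² and cell variance (1 − ρ) × 2.5²/cell size. The summed weight on the Basse-Normandie cells is the shift in the effect per 1-point regional difference. With 15 patients drawn:

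| ICC | Layout A | Layout B |
|---|---|---|
| 0.01 | 0.33 | 0.26 |
| 0.05 | 0.23 | 0.20 |
| 0.10 | 0.17 | 0.15 |

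Under layout A at ICC 0.05, the shift is 0.09 without period terms. A crude comparison of means gives 15/90 = 0.17. With a fixed Basse-Normandie effect it is 0.

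**4. Precision at ICC 0.05.** Standard error (SE) of the effect; power for a 2-point effect by normal approximation:

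| Basse-Normandie data | SE, layout A | Power, layout A | SE, layout B |
|---|---|---|---|
| None (five centres) | 0.71 | 0.80 | 0.63 |
| 15 drawn, random cluster (the plan) | 0.62 | 0.90 | 0.57 |
| All 80, random cluster | 0.51 | 0.98 | 0.50 |
| All 80, fixed Basse-Normandie term | 0.54 | 0.96 | 0.53 |

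**5. The cost of dropping the region.** The five-centre power of 0.80 is a normal approximation. With SE 0.713 and a t reference it is 0.76 at 19 degrees of freedom and 0.48 at 3. On the plan's own parallel formula, the variance of a cluster mean is 6.25 × 1.7/15 = 0.708. Three against three gives SE √(0.708 × 2/3) = 0.69 and power 0.83. Three against two gives SE √(0.708 × 5/6) = 0.77 and power 0.74.

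**The case against.** The region's special role is partly disclosed: Study design says that its staff are already trained and that only the other five clusters enter stepwise. That stands. However, the sample size still needs six clusters, and the primary objective still includes the 15 drawn patients.

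A reader might infer that the draw throws away 81% of the region's data (65/80). The documents do not support this. All 80 patients serve the Step 4 adherence test, and nothing limits the global model to the 15. The loss concerns the primary comparison only.

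A reader might also take 0.23 as the bias of the trial. It is a sensitivity per assumed 1-point difference, under assumed layouts and a random cluster effect. One point is large here: the between-cluster SD at ICC 0.05 is 2.5 × √0.05 = 0.56, so it is about 1.8 SD. A shift of 0.2 is a tenth of the 2-point target and about a third of the planned standard error.

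The cap of 15 could be defended as limiting the region's influence. At ICC 0.01 under layout A it does: the weight is 0.33 with 15 patients and 0.55 with 80. At ICC 0.05, the plan's value, it hardly does (0.23 and 0.26). A fixed term removes a constant regional shift altogether.

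Finally, a reader might conclude that the five centres alone must be the primary analysis. That is not required. An always-exposed cluster can properly inform period effects, and the five-centre analysis has little or no power to spare.

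**Conclusion.** The point holds. Basse-Normandie is a non-randomised, always-PEP cluster; five clusters can be randomised, not six; and the draw of 15 does not make the region comparable with the others. The structural part follows from Study design and Sample size calculation alone and needs no assumed figures.

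The size does rest on assumptions. With random clusters and period effects, the shift is about 0.2 points per 1-point regional difference (0.15 to 0.33 over ICC 0.10 to 0.01 and two layouts), and zero if that cluster has a fixed effect. The text does not say which applies. The arithmetic behind 90 and 230 is not in error, and the documents do not show that the region actually differs. The finding is about validity and clarity, and it can be repaired before analysis at little cost.

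**What to change.** - State that five clusters are randomised and that Basse-Normandie is a non-randomised cluster receiving PEP throughout. Correct the cluster count per arm in the Sample size calculation accordingly.
- Delete the draw of 15.
- In the primary period-adjusted mixed model, include all evaluable Basse-Normandie patients with a fixed Basse-Normandie effect, so that they inform only the period effects.
- Pre-specify an analysis of the five randomised centres alone as a sensitivity analysis, with a small-sample reference distribution.

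Cost: wording and model specification, with no new patients. At ICC 0.05 under layout A the standard error is about 0.54. That is slightly above the 0.51 for all 80 patients without the fixed term, but below the planned 0.62. The price is an assumption that period effects are common to all regions. The gain also needs Basse-Normandie to recruit across the same periods as the other centres. If its patients all fell in one period, the fixed term would absorb them and the standard error would return to the five-centre value of about 0.71. The Discussion describes evaluation at regional scale first and national scale second, so the overlap in time should be confirmed before the model is fixed.

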#### Data analysis

At every stage of the analysis, exploratory data will provide, for quantitative variables, mean, its standard deviation, median, quartiles, and missing data; for qualitative variables, frequencies and 95% confidence interval. Statistical tests and confidence intervals will be calculated with an overall error significance level of 5%. For the main objective (Step 5), statistical analysis will be done on the per-protocol population: it will concern assessable patients who have completed the whole program (3 sessions after the educational diagnosis).

Pain interference with daily life scores at 8 weeks post inclusion will be first compared between experimental PEP group and control group, in consideration of the correlation of data (generalized linear mixed model).

For the first secondary objective (Step 4), patients’ adherence to the PEP at the regional scale will be assessed using one-sided test comparing a proportion to a reference value.

For all the steps, a global analysis will be performed, taking into account the different periods of the study, clusters, and the care provided for each period, using a generalized linear mixed model for scales scores and for qualitative results obtained from questionnaires. This analysis will be adjusted to the patients’ demographic and clinical characteristics.

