### Study flowchart

For all the participants with signed consent form, assessments will be conducted at baseline and 8 weeks after inclusion (Fig. 2). For patients of the experimental PEP group, complementary assessments will be performed twice during the program.

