**Table 2 Tab2:**
[figure not shown]
Questionnaires and scales used to assess pain, educational impact and satisfaction with the PEP

^1^ Questionnaires will be filled during a visit to hospital or sent by post

^2^ At inclusion

^3^ For control patients, questionnaires will be addressed 8 weeks after inclusion

*Abbreviations: PEP* Pain Education Program

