#### Primary and secondary endpoints

The main judgement criterion in this study is the impact of pain on daily activities measured with the BPI. A score will be established by averaging the response on the 7 items of the subscale 9. The benefit of TPE on the impact of pain will be defined as a 2-point-decrease (on a scale of 10) between the values measured before and at the end of the PEP (at 8 weeks after inclusion). A 2-point decrease on the BPI scale correspond to a clinically significant improvement [32].

The first secondary endpoint is the proportion of patients adhering to the whole PEP (3 sessions), adherence being defined as the achievement of these 3 sessions for patients who undertook to follow them.

Other secondary endpoints are based on:

- Pain intensity and relief (BPI), its impact on QoL (subscale 9 of BPI, HADS), qualitative characteristics of pain (QDSA) and pain adherence.

- Patient’s knowledge and skills about pain, patient’s self-efficacy to actively manage pain, patient-reported impression of improvement.

- Participants’ satisfaction and educators’ satisfaction with PEP.

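### The primary (Step 5) analysis keeps only PEP patients who completed all three sessions, a filter that cannot apply to controls, so the comparison is no longer between the groups as allocated

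*Protocol article*

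**What the plan says.** Under Data analysis, the article fixes the population for the main objective: "statistical analysis will be done on the per-protocol population: it will concern assessable patients who have completed the whole program", with the programme specified as "3 sessions after the educational diagnosis". The comparison that follows is between arms: "Pain interference with daily life scores at 8 weeks post inclusion will be first compared between experimental PEP group and control group", using a generalized linear mixed model.

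Controls are recruited before their centre's staff are trained. Under Sample size calculation they need only be assessable, and the footnote to Table 2 says: "For control patients, questionnaires will be addressed 8 weeks after inclusion". No session requirement is attached to them.

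Completion of the same three sessions is also the first secondary endpoint, "adherence being defined as the achievement of these 3 sessions for patients who undertook to follow them" (Primary and secondary endpoints). For Step 4 it is tested in Basse-Normandie with p0 = 0.70 against p1 = 0.85.

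Under Study flowchart, for every participant with a signed consent form, "assessments will be conducted at baseline and 8 weeks after inclusion". The Objectives section states the aim as the effectiveness of the programme. The article names no analysis of all enrolled patients.

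**The concern.** A completion rule that only one arm can meet or fail is not a neutral definition of the analysis set. Whether a patient finishes three sessions is decided after the cluster's condition is set. In patients with cancer, uncontrolled pain and WHO performance status up to 2, it plausibly depends on fatigue, progression and motivation, which also bear on pain interference at 8 weeks. PEP patients who do badly can leave the analysis for not completing; comparable controls cannot leave it for that reason.

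Two things are at stake. The Discussion justifies the design by the control of confounding that cluster randomisation gives, and this filter surrenders part of that control. And a result in completers answers a different question from whether providing the programme improves pain management.

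**Working it through.** **1. Reproduce the planned size.** Inputs from Sample size calculation: difference 2 points, SD 2.5, ICC 0.05, 3 clusters per arm, two-sided alpha 5%, power 80%. A two-sample t-test needs n = 26 per arm without clustering. With k = 3 clusters per arm, the size per cluster is m = n(1 − ICC)/(k − n·ICC) = 26 × 0.95/(3 − 1.3) = 14.5, rounded up to 15. That is 45 per arm, as stated. The 45-per-arm figure follows from its inputs and is not at fault here.

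**2. Standard error implied by the plan.** Design effect = 1 + (15 − 1) × 0.05 = 1.70. SE = 2.5 × √(2 × 1.70/45) = 0.687. Power for 2 points (normal approximation) = Φ(2/0.687 − 1.96) = 82.9%.

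**3. Who can be removed.**

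| | PEP arm | Control arm |
|---|---|---|
| 8-week BPI needed | yes | yes |
| Three sessions needed | yes | no sessions exist |

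The first row applies to both arms; the second can act on one only.

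**4. Bias.** Let π be the completion share and D the mean 8-week BPI of non-completers minus that of completers. The completer mean equals the whole-arm mean minus (1 − π)·D, so with no true effect the filter shifts the difference by (1 − π)·D. A positive D favours PEP.

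The documents give no D, and no completion rate for the Step 5 centres. Assumptions: D = 1 to 2 points; 1 − π = 15% (the Step 4 target case) to 30% (its null case).

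Two-sided type I error = 1 − Φ(1.96 − b/SE) + Φ(−1.96 − b/SE), where b is the bias and SE = 0.687:

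| Non-completion | D | Bias b | Type I error |
|---|---|---|---|
| 15% | 1 | 0.15 | 5.5% |
| 15% | 2 | 0.30 | 7.2% |
| 30% | 1 | 0.30 | 7.2% |
| 30% | 2 | 0.60 | 14.1% |

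**5. Cross-check with another model.** Suppose completion follows a latent normal variable with correlation ρ to lower 8-week interference. Then b = ρ × 2.5 × φ(c)/π, with c = Φ⁻¹(π). For assumed ρ from 0.1 to 0.5, b is 0.07–0.34 points at 85% completion (type I error 5.1–7.9%) and 0.12–0.62 points at 70% (5.4–14.7%). The order of magnitude is the same.

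**6. Effect of removing the filter.** Assume a 2-point effect in completers and none in non-completers. The all-patient effect is 2 × 0.85 = 1.7 or 2 × 0.70 = 1.4 points. Power at 45 per arm is Φ(1.7/0.687 − 1.96) = 69.6% or Φ(1.4/0.687 − 1.96) = 53.1%. With 3 clusters per arm and the normal approximation, 80% power would need about 3 × 25 = 75 per arm or 3 × 96 = 288 per arm.

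**The case against.** **Direction and size are not documented.** This stands. Nothing in the article relates completion to outcome. Controls can also be lost if they do not return the 8-week questionnaire, and both arms require a life expectancy of at least 6 months and WHO status of 2 or less, which narrows the prognostic range. The direction is an expectation and the sizes are conditional. The one-arm rule itself does not depend on them.

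**30% non-completion is not a planning value.** Correct: 0.70 is the rate that Step 4 sets out to reject, and it concerns Basse-Normandie. The 15% rows are closer to what the protocol hopes for; the 30% rows are an upper case.

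**A global analysis is planned.** It adjusts for period, cluster and patient characteristics, which may reduce the bias. But it names no wider population, and adjustment for measured characteristics does not restore the randomised comparison.

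**Analysing everyone does not give perfect protection either.** True: patients consent after their cluster's condition is set, and Basse-Normandie receives PEP throughout because its staff were already trained. These limits come with the design; the completer filter adds an avoidable one.

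Three stronger readings are tempting and are not supported:

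- A reader might infer that about a third of null trials would be declared positive. That needs a standard error near 0.39, which does not follow from the protocol's figures for 45 per arm.
- A reader might infer that an apparent benefit could be wholly selection. A significant result under no effect becomes somewhat likelier, but the largest bias tabulated, 0.60 points, is far below the 2-point target.
- A reader might set the recruitment margin, "it is therefore planned to recruit 260 patients in order to anticipate some non-assessable patients" (30/260 = 11.5%), against 15–30% non-completion and conclude that recruitment must fall short. The text does not say how the 30 spare patients are shared among groups, Step 4 patients need no completion allowance because completion is their endpoint, and the powered comparison needs 45 per arm.

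**Conclusion.** The point holds as a defect of the stated primary analysis population. It is written into the article, so it is not a detail left to an unseen analysis plan. As worded, the definition either excludes every control or selects the PEP arm alone on a post-allocation event that the trial also reports as an outcome. Either way the primary result would not be a comparison of the groups as allocated, and would not estimate the effectiveness of offering the programme.

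Under the assumed 15–30% non-completion and 1–2 point difference, the bias is 0.15–0.60 points, with type I error about 5.5–14% at a standard error of about 0.69. These figures rest on assumptions that the documents neither supply nor contradict. Because the rule governs the main conclusion, it should be changed before analysis.

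**What to change.** In Data analysis, define the primary Step 5 population as all consenting patients with an 8-week BPI, analysed by the condition of their cluster at inclusion, whatever number of sessions they attended. Define assessable by availability of the 8-week BPI, not by session completion, and use that definition in the sample size section too. State that the global analysis uses the same population. Keep the three-session completer analysis as a labelled sensitivity analysis, and say which controls it is compared with.

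No new data collection is needed: the 8-week assessment is already scheduled for every consenting participant, at a hospital visit or by post, so it can be obtained from patients who stop attending.

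The cost is in power. The all-patient effect may be smaller than in completers: if non-completers gain nothing, 2 points becomes about 1.7 (85% completion) or 1.4 (70%), and power at 45 per arm falls from about 83% to about 70% or 53%. The sponsor should recheck and restate the power for the all-patient effect, giving the completion rate assumed.
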